**Fig. 1 Fig1:**
[figure not shown]
Flow diagram of study protocol

Following successful screening, enrolled participants will proceed with the rest of the baseline assessments. The participants will be subsequently randomised into either the active treatment group or waitlist control. Utilizing the Random Allocation Software version 2.0 [23], randomization will be stratified by gender by the study-coordinator.

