### Biomarkers analyses and statistical analyses plan

In the analyses of the biomarkers, aliquoted plasma will be used to measure the cytokines and metabolic profiles of the research participants using single-analyte enzyme-linked immunosorbent assay (ELISA). Using targeted approach, selected RNA targets, which may include messenger RNA and micro-RNA, for a subset of the subject will be analysed based on the data obtained from the cytokines and metabolic profiles. Whole bloods aliquoted on Trucount tubes are stained with a series of fluorescence-conjugated antibodies marking the surface receptors of immune cell. Using flow cytometer, part of the phenotyping includes classical markers of senescence, Cluster of differentiation 57 (CD57) and Killer-cell lectin like receptor G1 (KLRG1), exhaustion of T cells, Programmed cell death protein 1 (PD1) and potentially identification of subpopulations of B cells and myeloid cells with a focus on the pro-inflammatory cells. The extent of DNA damage repair will be assessed by flow cytometry as well. Other immuno-assays aiming at identifying markers or predictors of immune status to examine the effects of the interventions may be applied with the bio-banked samples.

In the data analyses procedures, statistical significance level will be set at .05 for all descriptive and statistical analyses. All analyses will be performed using the SPSS. Based on the initial condition assignment and using the last observation carried forward (LOCF) method, intention-to-treat analyses will be conducted. Preliminary analyses will be performed next to assess the influence of demographic factors that (age, gender, education level, marital status, etc.). Where necessary, these variables will be included as covariates or control variables in the analyses. As some attrition is expected between interviews, prior to data analysis, comparisons will be made of retained and non-retained participants, to determine whether there are any systematic differences.

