If there are chance imbalances in baseline participants’ characteristics, they will be entered as covariates in the analyses. Repeated Measure Analysis of Variance (ANOVA) will be used to examine the difference of the outcome between the active treatment group and waitlist control group over the 3 time points [42]. If there are imbalances in baseline participants’ characteristics, those variables will be included as covariates in the analyses. Additionally, dependent t-test will be employed to analyse the changes in scores within the active treatment group across the 3 time-points.

Ratios of selected biomarkers will be taken between cortisol, IL-6, CRP and DHEA-S. Additionally, fold changes and percentage changes would be performed. In the case of significant difference between the baseline measurements of prognostic demographic variables, multivariate regression will be performed when examining the differences between the means of the biomarkers for the two study arms. Correlation and/or heatmap analyses will be carried out to examine the relationships between the biomarker levels. On the aggregate biomarker level, principal component analyses (PCA) will be performed to examine the overall effect of the treatment. Mediational analyses employing bootstrapping technique will be employed to explore the mediating variables between the psychometric outcomes and biomarker levels.

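### Covariates are to be chosen from the trial data by baseline imbalance or an undefined need, and gender, the stratification factor, is not a fixed model term

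*Protocol article*

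**What the plan says.** All the covariate rules stand in the Protocol article, section on biomarker and statistical analyses. There are three.

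- **Imbalance, main analyses.** "If there are chance imbalances in baseline participants’ characteristics, they will be entered as covariates in the analyses". After the sentence on the ANOVA the rule appears again: "If there are imbalances in baseline participants’ characteristics, those variables will be included as covariates in the analyses". Neither sentence says what counts as an imbalance or which characteristics are examined.
- **Significance, biomarkers.** "In the case of significant difference between the baseline measurements of prognostic demographic variables, multivariate regression will be performed".
- **Influence, then need.** "Preliminary analyses will be performed next to assess the influence of demographic factors that (age, gender, education level, marital status, etc". The next sentence gives the consequence: "Where necessary, these variables will be included as covariates or control variables in the analyses". No criterion of need is stated.

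The model itself is described without fixed covariates: "Repeated Measure Analysis of Variance (ANOVA) will be used to examine the difference of the outcome between the active treatment group and waitlist control group". Baseline is one of its three time points. The same section says that the "statistical significance level will be set at .05 for all descriptive and statistical analyses".

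Under Recruitment and baseline procedures, after Fig. 1, the article states that "randomization will be stratified by gender by the study-coordinator". The analysis section does not commit to gender as a model term. It names gender only among the demographic factors whose influence is to be looked at.

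**The concern.** Under randomisation a baseline difference between arms is a chance event, as the first rule itself says. It is unrelated to whether the variable predicts outcome. A rule triggered by imbalance therefore selects on the wrong property: it passes over strong predictors that happen to be balanced and may admit weak ones that are not. The biomarker rule is confined to demographic variables regarded as prognostic, so it is less likely to admit an irrelevant one, but its trigger is still the baseline test.

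The third rule looks at influence, which is the relevant property, but it does so in the trial's own data and without a criterion. Nothing says which of the three rules governs when they disagree, or whether the covariate set may differ between outcomes.

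At stake are precision in a trial of 35 per arm, agreement between the analysis and the stratified allocation, and a p-value that keeps its nominal meaning. If the model can be settled after the arm comparison is visible, the last of these is not assured.

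**Working it through.** **Inputs.** Alpha .05 (analysis section; two-sided assumed). 70 participants, 35 per arm (Sample size). Gender as stratification factor. The plan gives no figure on covariates to reproduce. The 70 is a cited pilot-trial recommendation without effect size, SD or power, so it cannot be re-derived. Assumed here: imbalance read as p<.05, the share of variance explained (R²), the effect sizes, no dropout.

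**1. How often the imbalance rule acts.** Under randomisation each variable is flagged with probability .05, whatever its prognostic strength. For k independent variables, the chance that at least one is flagged is 1 − 0.95^k:

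- k = 4 (the number of demographic factors named): 1 − 0.8145 = 18.5%
- k = 10 (assumed): 1 − 0.5987 = 40.1%

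Correlated variables would change these figures.

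**2. Cost of omission in a post-baseline comparison between arms.** Variance inflation is 1/(1 − R²), and the information lost is worth 70 × R² participants:

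| R² (assumed) | Variance inflation | Equivalent loss |
|---|---|---|
| 10% | 1/0.90 = 1.11 | 7 of 70 |
| 20% | 1/0.80 = 1.25 | 14 of 70 |
| 30% | 1/0.70 = 1.43 | 21 of 70 |

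**3. Power under the rule.** Simulation, 10,000 runs, 35 per arm, one post-baseline outcome, true effect 0.5 SD (assumed), one covariate with correlation r to the outcome:

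| r | Unadjusted | Adjusted only if imbalanced | Always adjusted |
|---|---|---|---|
| 0.3 | 54% | 54% | 57% |
| 0.5 | 54% | 54% | 66% |
| 0.7 | 54% | 56% | 82% |

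The imbalance rule recovers almost none of the available gain. With no treatment effect, its rejection rate is 4.6%, 4.4% and 3.6%, so it errs towards caution.

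**4. Gender left out.** Same setting, gender balanced between arms, gender effect of 0.5 / 0.8 / 1.0 within-gender SD (assumed). Without gender, type I error is 4.8% / 3.6% / 2.9% and power 52% / 48% / 45%. With gender in the model they are about 5% and about 54%.

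**5. The group-by-time contrast.** Steps 2 to 4 concern a single post-baseline visit. The planned ANOVA includes baseline as a time point, and its group-by-time test compares changes within person. If a covariate shifts every visit by the same amount c, the change is (Y₁ + c) − (Y₀ + c) = Y₁ − Y₀, and the covariate cancels. In simulation with a baseline-to-follow-up correlation of 0.6 to 0.7 (assumed) and R² of 10% to 30%, the ratio of unadjusted to adjusted variance of the change contrast was 0.98 to 0.99, so adjustment gained nothing. The figures in steps 2 to 4 carry over only where the covariate predicts change.

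**6. What the undefined need permits.** Four candidate covariates give 2⁴ = 16 possible models. With 70 participants, no treatment effect and the most favourable of the 16 reported, simulated type I error was about 7%, 10% and 14% when the covariates together explained 0%, 20% and 30% of variance. One fixed model stays near 5%. This is the worst case that the wording allows.

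**The case against.** **Gender is a named candidate.** A reader might infer that gender is never adjusted for. The article does not support that, since gender is listed among the factors that may become covariates. What stands is that its inclusion is not guaranteed, and that the imbalance rules cannot be expected to select a factor balanced by design.

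**Prognostic variables have a way in.** A reader might also infer that they will mostly be left out. That holds for the imbalance and significance rules alone, and only if imbalance means p<.05. The influence route could admit them. It remains a choice made in the trial data without a criterion.

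**The threshold is assumed.** Only the biomarker rule speaks of significance. The blanket .05 level, which covers descriptive analyses too, makes that reading plausible for the main analyses but does not establish it.

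**The size depends on the contrast.** This objection stands in full: for group-by-time tests a stable covariate cancels, so the precision loss cannot be claimed for the whole plan.

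**A condensed article may leave covariates to the analysis plan.** That would excuse silence. Here the article states rules, and those rules are the problem.

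**Data were already collected.** Study progress reports data collection complete and analyses under way. One might infer that the rules were written, or a model picked, with arm-level results in view. The article gives a status at publication and no more. It shows that the choice was still open on paper, not that it was misused.

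**Conclusion.** The point holds as a fault in how the covariates are chosen. Three overlapping, data-dependent rules decide the adjusted model; two of them select on a property unrelated to prognosis, the third has no criterion, and the stratification factor is not fixed in the model.

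The size depends on the analysis. For a comparison between arms at a post-baseline visit, the variance penalty is about 11% to 43% for covariates explaining 10% to 30% of outcome variance, and omitting gender makes the test conservative. For the group-by-time contrast the loss is small unless the covariate predicts change. Error rates can move either way: slightly below .05 under the imbalance rule, and above it if the undefined route is used freely. Every such figure rests on assumed effect sizes and correlations, none of which the article gives.

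This should be corrected because it weakens precision and credibility. It does not invalidate the trial.

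**What to change.** - Before analysis, name one covariate set for all outcomes: gender as stratification factor, plus age and education level as collected. Include it whatever the observed balance. If some arm comparisons have already been run, say so and date the decision.
- Delete both imbalance sentences, the baseline-significance trigger for biomarkers and the undefined needs-based route. Label any imbalance-driven model a sensitivity analysis.
- Choose one treatment of the baseline outcome: keep it as one of the ANOVA time points, or model the 3- and 6-month values with the baseline value as a covariate. Do not do both.

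**Cost.** Age, gender and education are already collected at baseline. Gender, age and education as a linear score use 3 of about 68 degrees of freedom (70 − 2), leaving 65; education in several categories uses a few more. Otherwise the change is wording, unless the baseline value becomes a covariate, which changes the form of the model.

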### Trial design

This interventional study will be a RCT comparing participation in a HT program to being in a waitlist control. The intervention will lasts for 6 months with 1-h HT sessions during the first 3 months followed by monthly sessions the next 3 months. Outcome assessments will be conducted at baseline, 3 months and 6 months. The 3-months follow-up intervals were decided based on a study by Gonzalez et al. which found that participants’ depressive symptoms declined after 3 months and these improvements were maintained in the final 6-month follow-up [6].

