### Sample size

For a pilot RCT with continuous outcomes, the recommended total sample size is 70, with 35 in each study arm with relative change in outcome variables within 95% confidence interval [41].

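### The repeated-measures ANOVA treats the pre-randomisation baseline as one of three outcome time points, names no tested term and plans no adjustment for the baseline outcome, so it either dilutes the effect or loses precision

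*Protocol article*

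**What the plan says.** Under Biomarkers analyses and statistical analyses plan, the protocol article assigns the between-arm comparison to a repeated-measures ANOVA, used to examine the "difference of the outcome between the active treatment group and waitlist control group over the 3 time points". Trial design identifies the time points: "Outcome assessments will be conducted at baseline, 3 months and 6 months". Recruitment and baseline procedures sets the order. Enrolled participants complete the baseline assessments, and then "The participants will be subsequently randomised into either the active treatment group or waitlist control".

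Covariates enter only conditionally. Of demographic factors the plan says "Where necessary, these variables will be included as covariates or control variables in the analyses". Of participant characteristics found to be imbalanced at baseline it says "those variables will be included as covariates in the analyses". The baseline value of the outcome under test is not named as a covariate.

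On alpha, "statistical significance level will be set at .05 for all descriptive and statistical analyses". On size, "the recommended total sample size is 70, with 35 in each study arm". No effect size, SD, power or within-person correlation is given.

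**The concern.** Baseline precedes randomisation, so any arm difference there is chance. Making it a level of the outcome factor creates a problem that depends on which ANOVA term carries the efficacy claim, and the article does not say which.

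- **Group main effect.** The comparison averages a known zero with the two real differences and so understates the effect.
- **Group-by-time interaction.** The baseline is used properly as a reference, but only through change from it. That is less efficient than regressing the follow-up value on baseline.

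With 35 per arm there is little precision to spare. Leaving the term open also lets two tests with different meaning and different power fit the same sentence.

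**Working it through.** **Inputs from the article.** n = 35 per arm; alpha 0.05 (sidedness not stated, two-sided assumed); visits at baseline, 3 and 6 months; baseline before randomisation.

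**Assumptions, because the article gives no figures.** SD = 1 at every visit; the same correlation r between any two visits, from 0.4 to 0.7; true effect d = 0.5 SD at both month 3 and month 6; complete data.

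**Step 1: the plan's own figure.** The total of 70 comes from a recommendation for pilot trials, described as "with relative change in outcome variables within 95% confidence interval". It cannot be reproduced, since no effect, SD or power is stated. For scale, an unadjusted comparison at one visit has SE = √(2/35) = 0.239 SD. That gives about 55% power for 0.5 SD, and 80% power needs about 0.67 SD.

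**Step 2: group main effect over three visits.**
- Expected estimate: (0 + d + d)/3 = 2d/3 = 0.333 SD. With unequal effects it is (0 + d3 + d6)/3, still two thirds of their mean.
- Variance of a person's three-visit mean: (1 + 2r)/3. SE of the arm difference: √(2/35 × (1 + 2r)/3).
- r = 0.4: SE = √(2/35 × 0.600) = 0.185; 0.333/0.185 = 1.80; power 43%.
- r = 0.7: SE = √(2/35 × 0.800) = 0.214; 0.333/0.214 = 1.56; power 34%.

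**Step 3: group-by-time interaction (F on 2 and 136 df).**
- Noncentrality = (n/2) × Σ(d_t − mean)²/(1 − r).
- Deviations of (0, 0.5, 0.5) from their mean are −1/3, 1/6 and 1/6; the sum of squares is 0.1667; 17.5 × 0.1667 = 2.917.
- r = 0.4: 2.917/0.6 = 4.86; power 48%.
- r = 0.7: 2.917/0.3 = 9.72; power 79%.
- The effect is measured relative to baseline, so it is not diluted.

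**Step 4: like-for-like comparison at a single visit.**
- Change-score variance 2(1 − r); ANCOVA variance 1 − r²; ratio (1 + r)/2. The ratio is 0.70 at r = 0.4 and 0.85 at r = 0.7, so the ANCOVA variance is 30% to 15% smaller.
- r = 0.4: change SE = √(2/35 × 1.20) = 0.262, power 47%; ANCOVA SE = √(2/35 × 0.84) = 0.219, power 61%.
- r = 0.7: change SE = √(2/35 × 0.60) = 0.185, power 76%; ANCOVA SE = √(2/35 × 0.51) = 0.171, power 82%.

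Power by formula (noncentral t or F), with simulation of 6,000 trials per setting in brackets:

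| r | Group main effect | Group-by-time | Month 3, change score | Month 3, ANCOVA |
|---|---|---|---|---|
| 0.4 | 43% (44%) | 48% (49%) | 47% (47%) | 61% (62%) |
| 0.5 | 39% (39%) | 56% (57%) | 54% (54%) | 66% (65%) |
| 0.6 | 36% (36%) | 66% (66%) | 64% (63%) | 73% (72%) |
| 0.7 | 34% (34%) | 79% (79%) | 76% (75%) | 82% (81%) |

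From the simulation, the ANCOVA gain at one visit is about 14 points at r = 0.4 and about 5 points at r = 0.7.

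**Step 5: type I error.** In a separate simulation with no effect (3,000 trials per setting, r = 0.3, 0.5 and 0.7), rejection rates were 4.2% to 5.4% across the main effect, the interaction, and the change-score and ANCOVA analyses of the follow-up mean. No method is anti-conservative.

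**The case against.** The strongest reply is that the plan is valid and the dispute is about efficiency. Most of that stands, and it rules out several stronger readings.

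- **That the plan certainly dilutes the effect.** A reader might infer this from the wording about a difference between groups over three time points. The article names no term. Its hypothesis of greater improvement in cognitive functioning fits the interaction, under which nothing is diluted. The 34% to 44% figures belong to the main-effect reading only.
- **That the baseline is thrown away.** Under the interaction it is used through within-person change, only less efficiently.
- **That the fix raises power to 80% to 93%.** That range is for ANCOVA of the mean of months 3 and 6, a single 1-df contrast that gains from assuming a constant effect. Set against the 2-df interaction, it mixes the benefit of the covariate with the benefit of averaging. The single-visit comparison isolates the covariate.
- **That the ANOVA cannot give the arm difference at each visit.** It can, through arm-by-visit means and contrasts from the same fit. Which of these are tabulated may fairly be left to a fuller plan.
- **That the main or primary test is at fault.** The article names no primary outcome and no main test. This ANOVA is, however, the only general between-arm outcome test it describes.

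It could also be argued that imbalanced baseline characteristics might include the outcome itself. Even so, adjustment would depend on an observed imbalance and would not be pre-specified.

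The reply leaves two things unanswered: the tested term is open, and under either reading an available covariate that improves precision is not planned.

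**Conclusion.** The point holds as one of unclear specification and lost efficiency, not of validity. The pre-randomisation baseline is an outcome level, the tested term is unnamed, and the baseline outcome is not a planned covariate. The cost depends on the reading: an estimate shrunk by one third if the main effect is used, or a single-visit variance that ANCOVA would reduce by 15% to 30% if inference rests on change.

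The one-third dilution needs only a zero expected difference at baseline. The variance ratio needs equal variances at the two visits. The power figures rest further on d = 0.5 SD, sustained at both visits, equal correlations of 0.4 to 0.7 and no dropout, none of which the article supplies. With r above 0.7 the advantage of ANCOVA over change scores becomes small. The change should be made, but the existing plan would not produce false positives.

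**What to change.** Model only the month 3 and month 6 values as outcomes, in one mixed model with arm, visit, arm-by-visit, the baseline value of the same outcome, baseline-by-visit, and gender (the stratification factor). Make the baseline value a pre-specified covariate, whether or not an imbalance is seen. Name the contrast: if one overall test is wanted, use the arm difference averaged over both visits. Report the adjusted HT-minus-waitlist difference with a 95% CI at month 3 and at month 6.

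**Cost.** No new data are needed, since baseline values are already collected. There is a small downside. Study progress reports that data collection is complete and analyses are ongoing, so this is a late change. It must be dated, decided without reference to results by arm and documented, with the original ANOVA kept as a labelled sensitivity analysis and its tested term stated.

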**Methods/design:**

70 elderly participants aged 60 to 85 years old will be randomized to participate in either the active horticultural therapy group or be in the waitlist control. Sessions will be weekly for 12 weeks, and monthly for 3 months. Mental health will be assessed through self-reports of depressive and anxiety symptomatology, life satisfaction, social connectedness and psychological well-being, collaborated with immunological markers. Outcome measures of cognitive functioning and physical health include neuropsychological tests of cognitive function and basic health screening. Outcomes will be assessed at baseline, 3 months and 6 months post-intervention.

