### Intervention

The HT intervention is delivered in 1-h sessions, weekly in the first 3 months, followed by monthly sessions for the next 3 months (see Table 1). The extension of monthly sessions for 3 months is to determine sustainability and longer-term changes. Conducted by a trained practitioner and volunteer facilitators, the intervention is designed to cultivate an interest in gardening and promote relaxation. The participants will be assigned into groups of 7 with a facilitator for enhanced personal engagement. The participants will be with the same group members and facilitator throughout the intervention in order to build rapport and social connectedness. The facilitators are volunteers with the National Parks Board, who were trained with some basic knowledge of horticultural skills such as plant propagation, plant identification, flower arranging, houseplant care, and horticulture crafts. The essential element of the HT program is to communicate to the participants that plants are living things that must be given care. This caring extends the emotional growth of the participants.

**Table 1 Tab1:** Planned activity sessions for the 6 months of intervention

Session	Topic	Activity	Venue
1	Introduction	1. Familiarisation with research centre 2. Group formation 7/group 3. Indoor Gardening basics	Research Centre
2	Introduction	1. Garden familiarisation 2. Vegetables growing brief 3. Sowing vegetables seedlings	Chinese Garden
3	Wetland Walk	1. Park amenities familiarization 2. Interpretive walk 3. Reflection	Sungei Buloh Reserve
4	Introduction	1. Briefing for vegetables maintenance 2. Weeding and fertilizing vegetables plot	Chinese Garden
5	Nurturing	1. Briefing on pressed flowers 2. Material preparation 3. Make pressed flowers card	Research Centre
6	Nurturing	1. Garden maintenance briefing 2. Weeding, pruning, mulching garden/vegetables	Chinese Garden
7	Colour Walk	1. Park amenities familiarization 2. Interpretive walk 3. Reflection	Singapore Botanical Gardens
8	Nurturing	1. Vegetables maintenance 2. Compost making brief 3. Make compost	Chinese Garden
9	Harvest and Cook	1. Harvest vegetables 2. Hands on preparation for food 3. Sharing of cooked vegetables	Research Centre
10	Harvest and Cook	1. Seed sowing 2. Herbal plant brief 3. Herbal plants propagation	Chinese Garden
11	Festive Walk	1. Park amenities familiarization 2. Interpretive walk 3. Reflection	Gardens by the Bay (Flower Dome)

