For the gardening activities, they will be held fortnightly at the Chinese Garden where participants will be taught to do weeding and seed sowing. Such active participation in the natural environment has been found to improve mood state where participants were less stressed and were invigorated by their experiences [7]. Vegetables such as ladyfinger, milk cabbage, and choy sum will be planted by the participants. They will be educated on the making of fertilizer as well as knowledge on herbal plants. When their vegetable crops are ready for harvest, the participants will be able to prepare a soup dish together to encourage social connectedness amongst them.

Throughout the intervention programme, there will be an emphasis on education and mental stimulation whereby the facilitation is structured in terms of a series of questions and answers. This encourages active discussion amongst the facilitators and participants and social engagement. Longitudinal studies on mental stimulation and socially integrated lifestyle in late life have been found to have beneficial effect on cognition [24]. In closing each session, participants are asked for their reflection and verbal feedback.

The waitlist control will be assessed at the same time-point as the active treatment group but will only receive the same intervention program 6 months later.

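### Paired t-tests in the HT arm alone, planned beside the between-arm ANOVA, cannot separate an HT effect from change common to both arms, notably cognitive retest gain

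*Protocol article*

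**What the plan says.** The section Biomarkers analyses and statistical analyses plan describes two analyses of the outcome scores. The first is a repeated measures ANOVA that "will be used to examine the difference of the outcome between the active treatment group and waitlist control group over the 3 time points". The second, introduced as an addition, is that a "dependent t-test will be employed to analyse the changes in scores within the active treatment group across the 3 time-points". The same section states that the "statistical significance level will be set at .05 for all descriptive and statistical analyses". It names no corresponding test for the waitlist arm and does not call the within-arm tests descriptive or exploratory.

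Three other places matter. The hypotheses at the end of the Background are comparative: HT against waitlist. The Intervention section says "The waitlist control will be assessed at the same time-point as the active treatment group", so concurrent control data exist at every visit. The cognitive section lists performance tests (MoCA, RAVLT, Digit Span, Colour Trails, Block Design, semantic fluency), and Trial design places outcome assessments at baseline, 3 months and 6 months.

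On timing, the abstract says "Outcomes will be assessed at baseline, 3 months and 6 months post-intervention", whereas Trial design describes an intervention that itself lasts 6 months. The Intervention section says "The extension of monthly sessions for 3 months is to determine sustainability and longer-term changes".

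**The concern.** A paired t-test in one arm asks whether that arm's mean changed. It does not ask whether the arm changed more than it would have without HT, which is what the hypotheses claim. Anything that moves both arms alike (practice on repeated tests, season, familiarity with the research centre) enters the HT-only test in full and cancels only when the waitlist change is subtracted.

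Retest gain is a concrete threat here because the same performance-based instruments are outcomes at three visits. If the group-by-time comparison shows nothing for a cognitive test, a significant within-HT p-value at the pre-stated 0.05 level would still be available to report as improvement, with no waitlist result beside it. The month-3-to-month-6 paired test has the same weakness: a stable or rising score in the HT arm alone does not distinguish maintained benefit from a trend that the waitlist shares.

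**Working it through.** **Inputs from the protocol article.** The Sample size section says "the recommended total sample size is 70, with 35 in each study arm", so n = 35 in the HT arm. The level is 0.05; sidedness is not stated, so two-sided is assumed. There are three visits. The article states no error rate for the paired tests, so there is no figure of its own to reproduce.

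**Inputs assumed, because the article gives neither.** A gain common to both arms of g = 0.2 to 0.3 SD, and a correlation between visits of r = 0.6 to 0.8. The true HT effect is set to zero.

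**Paired test in the HT arm.** With equal SDs at the two visits, the SD of change is SD × √(2(1 − r)). The standardised mean change is therefore dz = g / √(2(1 − r)), and the test statistic is noncentral t with 34 degrees of freedom and noncentrality dz × √35.

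Example, g = 0.2 and r = 0.6: dz = 0.2 / √0.8 = 0.224; noncentrality = 0.224 × 5.916 = 1.32; probability of p < 0.05 = 0.251.

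Example, g = 0.3 and r = 0.8: dz = 0.3 / √0.4 = 0.474; noncentrality = 0.474 × 5.916 = 2.81; probability = 0.778.

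| Common gain | r = 0.6 | r = 0.7 | r = 0.8 |
|---|---|---|---|
| 0.2 SD | 0.251 | 0.318 | 0.444 |
| 0.3 SD | 0.487 | 0.605 | 0.778 |

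**Outside that range.** With g = 0 the probability is 0.05 whatever r is, so the test is valid for its own narrow question. With g = 0.1 it is 0.089 (r = 0.5) to 0.149 (r = 0.8).

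**Fewer participants.** The plan notes "As some attrition is expected between interviews" but gives no rate. With n = 30 and g = 0.2, the probability is 0.185 (r = 0.5) to 0.388 (r = 0.8). The problem shrinks somewhat but remains.

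**Between-arm test of change.** For two visits the group-by-time interaction equals a two-sample t-test on change scores. In 20,000 simulated trials with 35 per arm, the same gain of 0.2 or 0.3 SD in both arms and r of 0.5, 0.7 or 0.8, this test rejected in 4.5% to 5.4% of trials. The paired HT test in the same simulated data rejected in 21% to 78%, in line with the formula.

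**Timing.** Twelve weekly sessions are followed by three monthly sessions within the 6-month programme. The month-6 visit therefore falls at the end of the programme, not 6 months after it.

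**The case against.** The strongest reply is that the valid analysis is already planned. The ANOVA comes first, it compares the arms over all three visits, and it removes any shift common to both. The paired tests are additional, and they correctly answer whether HT-arm scores changed. All of this stands. A reader might infer that the plan abandons the randomised comparison, or that it states within-arm change will be counted as an HT effect. The document says neither; the second is a risk at the reporting stage. What the reply does not remove is that these tests carry the ordinary 0.05 level, have no waitlist counterpart and bear no descriptive label.

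A reader might also look to regression to the mean, since MoCA has an entry cut-off. That does not support a false gain. The rule is a lower limit of 22, so it excludes low scorers and the expected change on retest is downward. With an assumed mean of 24 to 26, SD 3 and reliability 0.7 to 0.9, it is about −0.05 to −0.39 points. No entry threshold is set on the depression, anxiety or well-being scales or on the biomarkers.

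Nor should the inflated rate be multiplied across every outcome and every pair of visits. Retest gain is argued only for the cognitive performance tests. It has no evident counterpart for height or blood pressure, and the biomarkers have their own analysis paragraph. Finally, how multiplicity is handled among supplementary tests may be settled in an analysis plan not shown here, so the point does not rest on it.

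**Conclusion.** The concern holds in a limited form. The HT-only paired t-tests are a stated choice of analysis that cannot support a claim about HT, although the data for the right contrast are collected at the same visits. For a cognitive outcome with a common gain of 0.2 to 0.3 SD and retest correlation of 0.6 to 0.8, each baseline-to-follow-up test would be significant in about 25% to 78% of trials with no HT effect, against about 5% between arms. The size rests wholly on those assumed values: at 0.1 SD it is 9% to 15% (correlation 0.5 to 0.8), and with no common shift it is 5%. The planned ANOVA is unaffected, and no sample-size figure changes. The abstract's wording on the 6-month visit is a separate, minor inconsistency.

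**What to change.** Replace the HT-only paired t-tests, as inference, with three HT-minus-waitlist contrasts from the planned repeated measures model: change from baseline to month 3, change from baseline to month 6, and change from month 3 to month 6, each with a 95% confidence interval. Report within-arm means and changes for both arms side by side, descriptively and without p-values. State that all claims about HT rest on the group-by-time comparison.

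As a minor edit, reconcile the abstract's description of the 6-month assessment with Trial design, and describe month 6 as the end of the monthly phase.

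The cost is wording in the analysis plan and report. The contrasts come from a model that is to be fitted anyway, and no new data are needed. The Study progress section says data collection is complete and analyses are under way, so the change should be dated and recorded as made at that stage.
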